This can have a psychological impact on the patients, with an alteration of the self-image causing anxiety, that can go as far as the social isolation of the patients. This can also give the family a negative image of the care given to the patient and goes against the notion of "taking care" which is at the heart of the nurse's role.

There are several types of lesions encountered in the peri-oral area: skin lesions, mucosal lesions and shearing/cuts. The pressure associated with the presence of ETT fixation systems is exerted over a prolonged period of time (on average 7 to 10 days for patients ventilated more than 48 hours). In addition, patients are frequently unable to move the tube in case of discomfort or to express their pain or discomfort (initial coma, deep sedation, etc.). There are risk factors for the development of pressure ulcers in severe resuscitation patients such as: sedation, decreased tissue perfusion, malnutrition, patients on vasopressors (6). Approximately 36% of ICU patients develop this type of peri-oral lesions during their hospitalization according to the prospective observational study conducted in 2011 under the aegis of the Société de Réanimation de Langue Française (7). Moreover, half of the lesions observed in this study appear between D1 and D5 of the hospitalization in intensive care unit.

The description of these lesions is done by the nurse who currently uses the NPUAP pressure ulcer scale to follow the evolution of the lesions. However, this scale cannot be used to follow the evolution of mucosal lesions. Indeed, these lesions are of a different nature, they do not have the same histological characteristics and the healing process differs (8). The "ROMPIS" scale was recently developed to evaluate mucosal lesions according to a classification allowing a better management of these specific lesions according to their stage (9).

Injuries related to these fixation systems develop for several reasons. First, the intubation tube is usually made of a rigid material that can cause friction or pressure on the underlying soft tissue. The adhesive tapes used to secure these devices can also irritate sensitive skin, and the cord can cause shearing or cutting, especially in the presence of edema, which is often the case in the ICU.

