### **2.2. SECONDARY OBJECTIVES AND EVALUATION CRITERIA**

#### **2.2.1. Secondary Objective(s)**

- Verify the effectiveness of the device in maintaining the endotracheal tube in terms of self-extubation from intubation until extubation or D28.
- Verify the effectiveness of the device in maintaining the endotracheal tube in terms of repositioning the tube from intubation until extubation or D28.
- Compare the time to the first peri-oral lesion from intubation to extubation or D28.
- Compare the intensity of peri-oral skin lesions assessed by nurses from intubation till extubation or D28.
- Compare the intensity of mucosal peri-oral lesions assessed by nurses from intubation till extubation or D28.

- Assessing the incidence of peri-oral lesions
- Evaluate the impact of the intervention on the maximum number of lesions per day.

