### **2.2.2. Secondary endpoint(s)**

- Number of self-extubations
- Number of significant repositioning of the endotracheal tube performed following a movement of more than 2 cm from the initially set marker.
- Time to the first peri-oral lesion from the time the patient is intubated until extubation.
- Assessment of the grade of cutaneous peri-oral lesions by the NPUAP scale.  
If several lesions co-exist, the lesion with the most severe grade will be retained.
- Evaluation of the intensity of the mucosal peri-oral lesions by the ROMPIS scale. If several lesions co-exist, the lesion with the most severe grade will be retained.
- Number of patients with at least one peri-oral lesion per 1000 ventilation days
- Maximum number of lesions per day

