#### Secondary criteria

The number of self-extubations, repositioning of the ETT will be estimated and compared using a Poisson regression model taking into account the study design. An offset of the logarithm of the intubation time will be included in the model.

The time to the first peri-oral lesion will be estimated using a random-effects survival model to account for the study design.

The time to onset will be calculated from the date of intubation to the date of first lesion onset. Patients for whom no lesion appeared will be censored at the date of extubation or at the date of discharge from intensive care or at D28. Patients who died will be censored at their date of death.

The grade of skin lesions (NPUAP scale) and mucosal lesions (Rompis scale) will be collected for each lesion. If the patient has no lesions, a grade=0 on the corresponding scale will be retained. If a patient presents several lesions, the maximum grade observed will be retained.

An ordinal logistic regression model controlling for intubation time and study design will be applied to compare both types of fixation.

The incidence of peri-oral lesions (expressed per 1000 ventilator days) will be calculated and described in each group: number of patients with at least one lesion / total number of ventilator days (up to 1ère lesions in patients with one lesion)

The maximum number of injuries per day will be estimated and compared using a linear model taking into account the study design.

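### Time to first lesion censors extubation and death: the hazard ratio stands as a cause-specific contrast, but any median time or cumulative risk from it would describe patients who stay intubated

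*Protocol*

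**What the plan says.** The objective in Protocol section 2.2.1 is "Compare the time to the first peri-oral lesion from intubation to extubation or D28". Section 2.2.2 defines the endpoint as "Time to the first peri-oral lesion from the time the patient is intubated until extubation".

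Under Secondary criteria in section 6.2.1 the analysis is: "The time to the first peri-oral lesion will be estimated using a random-effects survival model to account for the study design". The clock starts at intubation. On censoring, the text reads "Patients for whom no lesion appeared will be censored at the date of extubation", with discharge from intensive care and D28 as the other end points, and "Patients who died will be censored at their date of death".

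The protocol mentions neither competing events nor a cumulative incidence function. It also does not say which output of the survival model will be reported: hazard ratio, median or curve.

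The background in section 1.1 gives the duration of tube exposure as "on average 7 to 10 days for patients ventilated more than 48 hours".

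**The concern.** By the protocol's own definition the endpoint is a lesion that appears while the oral tube is in place. Final removal of the tube and death therefore end the possibility of the event. They are not losses to follow-up after which the lesion might still occur unobserved. Ordinary censoring treats the patients removed in this way as if they went on with the same lesion hazard as those still intubated.

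That does no harm to a hazard ratio that is read as cause-specific. It does matter for anything on the absolute scale. A median time, or a risk by D28, would answer a question about patients who are never extubated and never die. With a mean tube time far shorter than the 28-day window, most patients leave the risk set through these events, so the gap would be wide. A median could even be printed for an arm in which fewer than half of the patients ever have a lesion.

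The two fixation systems may also differ in how often the tube is lost, since self-extubation is itself a secondary endpoint. A curve that censors tube removal cannot show what such a difference does to the lesion risk that patients actually face.

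**Working it through.** **The plan's own figure.** The protocol states none for this analysis. Its 768 belongs to the primary endpoint and is consistent with its inputs: 185 per arm for 35% against 20%, times the design effect 1 + 23 × 0.10 − 24 × 0.05 = 2.1, times 2 arms = 777 (760 with unpooled variance).

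**Inputs from the protocol**
- Lesion risk 35% (cord and sheath) and 20% (tape): section 6.2.2. Taken here as risks by D10, the horizon of the primary endpoint.
- Mean tube time 7 to 10 days: section 1.1.
- Follow-up to D28: section 2.2.1.

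**Assumptions (not in the protocol)**
- Tube time is exponential with mean D = 7, 8.5 or 10 days, with or without a 2-day minimum, and independent of the lesion process. Death is included in the end of tube time.
- The lesion hazard is constant, or decreasing (Weibull, shape 0.7).

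**Formulas.** Let H(t) be the cumulative lesion hazard, h(t) its derivative, and G(t) the probability that the tube is still in at t.
- Real cumulative incidence: CIF(t) = ∫₀ᵗ h(u) exp(−H(u)) G(u) du.
- Censored-model risk: 1 − KM(t) = 1 − exp(−H(t)).
- With constant hazard h and μ = 1/D: CIF(t) = h/(h+μ) × [1 − exp(−(h+μ)t)].

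**How many leave.** Without a minimum, the share with the tube still in at D28 is exp(−28/D): 1.8%, 3.7% and 6.1% for D = 7, 8.5 and 10.

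**One case in full: D = 8.5, constant hazard, no minimum (μ = 0.1176)**
- Cord: CIF(10) = 0.35 gives h = 0.0804. CIF(28) = 0.0804/0.1980 × [1 − exp(−5.54)] = 40.4%. 1 − KM(28) = 1 − exp(−0.0804 × 28) = 89.5%. Censored-model median = ln 2/0.0804 = 8.6 days.
- Tape: CIF(10) = 0.20 gives h = 0.0397. CIF(28) = 24.9%. 1 − KM(28) = 1 − exp(−0.0397 × 28) = 67.1%.
- Cause-specific hazard ratio, tape to cord: 0.0397/0.0804 = 0.49. Crude risk ratio at D10: 0.20/0.35 = 0.57. The two differ because they answer different questions. Neither is wrong.

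**All 12 scenarios, risks fixed at D10**

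| | Real CIF | 1 − KM |
|---|---|---|
| Cord, D10 | 35% | 44-60% |
| Tape, D10 | 20% | 26-36% |
| Cord, D28 | 37-42% | 69-92% |
| Tape, D28 | 21-26% | 45-71% |

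The excess at D28 is about 30-53 points for cord and 22-48 points for tape. At D = 8.5 the censored-model median for cord is 8.6 to 12.2 days, although only 38-40% of cord patients have a lesion by D28.

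**Sensitivity.** If 35% and 20% are taken as risks by D28 instead, 1 − KM(28) is 63-88% (cord) and 40-64% (tape). The protocol also reports that "half of the lesions observed in this study appear between D1 and D5 of the hospitalization in intensive care unit". A piecewise hazard placing 50%, 70% or 80% of lesions by D5, again with the risks fixed at D28, gives 62-96% and 36-70%. The direction is the same in every case.

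**The case against.** The best defence is that the protocol does not plan the misleading output. Section 2.2.1 asks for a comparison between arms from intubation to extubation or D28, and section 6.2.1 says that all criteria will be compared. The natural product of a random-effects survival model is a hazard ratio. Censoring at extubation and death is the standard way to obtain a cause-specific hazard ratio, which fits an endpoint confined to the time with the tube in place. Which summaries go with the model may be settled in the analysis plan. This stands, and it limits the point.

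A reader might infer that the trial will report lesion risks at two or three times their real size. The documents do not support that: no Kaplan-Meier curve, median or D28 risk is named. Absolute risk comes from the primary percentage by fixation type, which this censoring does not touch, and from the rate per 1000 ventilator days. A mismatch with the primary percentage would not by itself prove an error either. The primary endpoint is adjudicated on photographs to D10, while lesions after D10 can only come from the nurses' examination.

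Nor does every extubation end the risk. Section 4.3 follows patients to the final extubation and re-intubations are recorded, whereas section 6.2.1 does not say which extubation censors. A patient discharged from intensive care still intubated remains at risk, so censoring there is ordinary.

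What remains is that section 6.2.1 does more than leave the matter open. It fixes the censoring rule and says that the time itself will be estimated. An estimated time under that rule is a median or a curve for patients who stay intubated, and nothing in the text restricts the output to a hazard ratio.

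**Conclusion.** The point holds in a limited form, as a cheap improvement to one secondary analysis. Extubation and death are frequent competing events that the protocol treats as ordinary censoring. The hazard ratio is a valid cause-specific comparison. It should not be read as an effect on cumulative lesion risk if tube time or mortality differs between arms.

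Any absolute time or risk from the same model would be far from what patients experience: at D28 about 69-92% against 37-42% for cord, and 45-71% against 21-26% for tape. These sizes rest on exponential tube times independent of the lesion process, on the protocol's mean of 7 to 10 days, and on reading 35% and 20% as D10 risks. They measure an output that the text permits but does not name. They are not the error of a planned result.

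**What to change.** In section 6.2.1, under Secondary criteria:

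1. Keep the random-effects survival model and call its result a cause-specific hazard ratio.
2. Give any absolute time or risk, by arm, as the Aalen-Johansen cumulative incidence of first lesion at D10 and D28. Treat final removal of the oral tube and death as competing events, and discharge from intensive care while still intubated as ordinary censoring.
3. Do not give one minus Kaplan-Meier or a Kaplan-Meier median for this endpoint.

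A subdistribution hazard ratio may be added but is a matter of preference. The schedule and source-data list do not show that the date of a tracheostomy during the stay is collected, so that date should be confirmed before it is used as a tube-removal date.

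The cost is a few sentences and slightly more analysis work, using dates that the censoring rule already needs and the final extubation that already ends follow-up. Absolute secondary risks will come out lower than a Kaplan-Meier display would show. The primary analysis and the sample size of 768 do not change.

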### **6.2.2. Statistical justification of the number of inclusions**

The study will take place in 16 centers (clusters) over two 12-month periods.

According to the IDEFIX study (7), we hypothesize that 35% of patients with a "cord and sleeve" fixation system have a peri-oral lesion compared to 20% with the elastic adhesive tape system.

The calculation of the number of subjects needed must take into account the design of the study and thus the two intra-class and inter-class correlation coefficients (15)

As we have no data on the estimation of correlation coefficients, we have retained, for the calculation of the number of subjects, a "moderate" intra-class correlation coefficient and therefore defined at 0.1, and as recommended, an inter-class correlation coefficient equal to half of the intra-class correlation coefficient, i.e. 0.05 (16)

With 90% power and 5% alpha risk, we calculated that each of the 16 centers would need to include an average of 24 patients per period.

A total of 768 patients are to be included.

### **6.2.3. Expected level of statistical significance**

The alpha risk is set at 5%.

### **6.2.4. Statistical criteria for termination of research**

NA

### **6.2.5. Method of accounting for missing, unused or invalid data**

These are patients hospitalized in an intensive care unit. The risk of missing data is a priori very low.

In all cases, the missing data will be presented for each of the 2 periods according to the sequence (cord fixation system then adhesive strips // adhesive strips fixation system then cord). The reasons for the missing data will be researched and also presented.

For the analysis of the main criterion (appearance of a lesion), in case of missing data on the expert assessment on photo, we will impute this data by the nurse's assessment. A sensitivity analysis will be applied on the imputation of missing data by considering that the patient did not present a lesion (whatever the period and the type of fixation used).

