#### **2.1.2. Primary endpoint**

Appearance of at least one peri-oral lesion during the first ten days of maintaining the orally inserted endotracheal tube.

The peri-oral lesion will be validated on photographs by an independent review committee. The photos will be taken daily, taking the precaution that the fixation system is not visible (maintaining the blindness for the adjudication committee) from D0 to D10.

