## Follow-up

During the two recruitment periods, a logbook will be given to the paramedical staff and will include the follow-up of each change of fixation made during their stay in the ICU.

The notebook will also record the presence of vasopressors, prone positioning, extubation or re-intubation, or the presence of sedation, which are risk factors for injury in resuscitation patients.

The nurse in charge of the patient will have to change the fixation system at least once a day and if necessary during the day in case of soiling or examinations.

Duoderm-type dressings used to prevent pressure sores under the endotracheal tube will not be accepted, since this is the subject of the study. However, it can be applied as a curative measure if a lesion appears.

A verification of the correct positioning of the endotracheal tube thanks to the graduated marker will be systematically carried out once a day. If a repositioning is necessary the nurse will note the number of centimeters (either at the bottom or at the top). The mobilization of the tube (change of side) will be performed according to the usual practices of the service.

The number of mobilizations, interventions (e.g., retying the knot) on the fixation system and the number of fixation system changes will be recorded daily.

The presence or absence of lesions will be assessed daily by the nurse in charge of the patient. She will also assess the type of lesion: cutaneous or mucous and depending on the type will use the appropriate scale to assess the grade: NPUAP scale (cutaneous) or / and the ROMPIS scale (mucous).

Two photos (one with the lower lip visible and one with the upper lip visible) will be taken every day by the nurses from the day of the first fixation change = D0 until D10. In no case will the whole face of the patient be taken. The patient will not be identifiable. The photos will be taken without the fixation visible to allow the blind to be kept for the committee that will evaluate the photos. The photos will be identified only by the patient's number and the date.

Each expert will have to record the presence or not of a peri-oral lesion between D0 and D10 of maintenance of respiratory assistance via an endotracheal tube. .

For the primary endpoint, we selected a daily photo assessment until D10. The choice of this time frame was based on:

- the time of appearance of peri-oral lesions (more than 50% of them appear during the first 5 days) (7)

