#### Adjudication Committee:

Several dermatologists and 2 nurses independent of the study will compose the adjudication committee. Each file (including all the photos of the same patient) will be randomly transmitted to each member of the adjudication committee. The members will rule on the presence or

absence of a lesion. If there is a discrepancy between the opinions of the committee members (if at least one of the experts disagrees with the other two), the committee will meet to discuss the matter and decide together whether or not the lesion is present.

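### Section 6.2.5 fills missing blinded committee verdicts with the unblinded nurse's assessment in the primary analysis, and the one sensitivity analysis it names is a weak check on that substitution

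*Protocol*

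**What the plan says.** **Endpoint.** Section 2.1.2: "The peri-oral lesion will be validated on photographs by an independent review committee". The photographs are to be framed so that the fixation is not seen, with the stated aim of "maintaining the blindness for the adjudication committee". The Follow-up text of section 4.3 repeats this: "The photos will be taken without the fixation visible to allow the blind to be kept for the committee that will evaluate the photos". Section 4.5.1 has the committee members rule on presence or absence of a lesion from the patient's file of photographs.

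**Bedside assessment.** Section 4.1 describes the study as open. Under Follow-up in section 4.3, "The presence or absence of lesions will be assessed daily by the nurse in charge of the patient", and also "The nurse in charge of the patient will have to change the fixation system at least once a day". Nurses take the photographs as well.

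**Missing verdicts.** Section 6.2.5 provides that "in case of missing data on the expert assessment on photo, we will impute this data by the nurse's assessment". It names one sensitivity analysis, which handles the missing data by "considering that the patient did not present a lesion (whatever the period and the type of fixation used"). It expects very little missing data, without giving a figure, and says that missing data and their reasons will be presented by period and sequence.

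**The concern.** The committee exists because the people at the bedside cannot be blinded. For every patient without a committee verdict, section 6.2.5 gives up that protection in the primary analysis. It enters the nurse's assessment as though it were a committee verdict.

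The two assessments differ in two ways. The nurse knows the arm, so expectation can influence the call. The nurse also examines the patient and grades on the NPUAP and ROMPIS scales. The first NPUAP stage (section 4.5.1) includes skin temperature, tissue consistency and sensitivity, none of which a photograph shows. Even an unbiased nurse may therefore record lesions that the committee would not. The protocol makes no allowance for such disagreement.

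If nurse–committee disagreement differs between arms, a spurious difference enters the one endpoint designed to be blinded. The question is then how large it could be and how well the named sensitivity analysis guards against it.

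**Working it through.** **Inputs from section 6.2.2.** Lesion rates 35% (cord and sheath) and 20% (adhesive tape), a 15-point difference; alpha 5%; power 90%; intra-class correlation 0.10; inter-class correlation 0.05; 16 centres with 24 patients per period, so 384 per arm and 768 in total.

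**Inputs not in the protocol, assumed here.** The fraction f of patients without a committee verdict, taken as 2% to 20% and equal in both arms unless stated. The between-arm difference D in net nurse misclassification (nurse rate minus committee rate, cord minus tape), taken as 10 to 30 points. Verdicts are taken as missing independently of lesion status. The calculation uses a normal approximation on the risk-difference scale, not the planned logistic model.

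**1. Reproduce the plan's figure.** Design effect = 1 + (24 − 1) × 0.10 − 24 × 0.05 = 2.1. Under individual randomisation, two-sided, the requirement is 185 per arm (pooled variance) or 181 (unpooled). Multiplied by 2.1 this is 388.5 or 380 per arm, a total of 777 or 760. Both agree closely with 768. Power at 384 per arm is 89.8%. The sample size is sound on its own inputs. It is used here for the 15-point yardstick and for the effective size, 384 / 2.1 ≈ 183 per arm.

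**2. Bias from nurse substitution.** Bias = f × D. The last column is the two-sided rejection rate when the true rate is 27.5% in both arms (no effect).

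| f | Patients of 768 | Bias, D = 10 to 30 points | Rejection rate (nominal 5%) |
|---|---|---|---|
| 2% | about 15 | 0.2 to 0.6 points | 5.0 to 5.2% |
| 5% | about 38 | 0.5 to 1.5 points | 5.1 to 6.2% |
| 10% | about 77 | 1 to 3 points | 5.5 to about 10% |
| 20% | about 154 | 2 to 6 points | 7.1 to 25% |

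As a share of the planned 15 points, 1.5 points is 10% and 6 points is 40%.

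**3. What the all-no-lesion analysis does.**
- *Nurse bias.* No nurse verdict is used. With equal f and no true effect, the difference is 0.275 × (1 − f) − 0.275 × (1 − f) = 0, so the nurse bias is removed.
- *Dilution.* A true 15-point difference becomes 15 × (1 − f): 14.25 points at f = 5%, 13.5 at 10%, 12 at 20%. Power falls to about 88%, 85% and 79%. If the result weakens relative to the primary analysis, dilution and removal of nurse bias cannot be told apart.
- *Unequal missingness.* With no true effect, 10% missing on cord and 20% on tape, the rates are 0.275 × 0.90 = 24.75% and 0.275 × 0.80 = 22.0%. That is a spurious 2.75 points favouring tape. Reversing the fractions gives 2.75 points favouring cord.
- *Arm-specific assumptions.* One value is assigned to everyone, so no scenario in which missing verdicts differ by arm is examined.

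**The case against.** **The substitution is checked.** A reader might infer that detection bias enters with no test and could not be revealed. The documents do not support this. The all-no-lesion analysis discards every nurse verdict and applies one rule to both arms, so a result resting on those verdicts should shift. This stands: the check exists, and the criticism is of its strength.

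**Missingness should be rare.** Section 6.2.5 expects very little, and two photographs a day are planned from D0 to D10. At 2–5% missing the bias is negligible. This stands as far as it goes, but the protocol gives no figure. Its stated reason, that patients are in intensive care, does not address absent or unreadable photographs.

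**Reporting and design help.** Missing data will be shown by period and sequence, which in this crossover identifies the arm, so unequal missingness would be visible. Every centre delivers both systems and centre is a fixed effect (section 6.2.1), so stable differences in calibration between centres largely cancel. Both points stand. Neither corrects an arm-specific tendency in the nurses' calls, whose direction and size the documents do not establish.

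**Files with some days missing.** A reader might infer that a file lacking some days' photographs, with no lesion on the rest, is automatically scored as lesion-free. Section 4.5.1 says "Each file (including all the photos of the same patient) will be randomly transmitted to each member of the adjudication committee" and asks for presence or absence, but does not say how missing days are treated. Section 6.2.5 does not say whether a missing assessment means a whole file or a single day. Nothing is concluded here on that point.

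**Analysis-plan territory.** Imputation detail is often left to the statistical analysis plan. Here, however, the protocol itself fixes the primary-analysis rule, and it is that rule which is questioned.

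**Conclusion.** The point holds in a limited form. Section 6.2.5 places unblinded nurse assessments in the primary analysis of a blinded endpoint wherever the committee verdict is missing. The single named sensitivity analysis is a real but weak check.

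The size depends on two quantities that the protocol does not give. With D assumed at 10 to 30 points and equal missingness, the bias is 0.2 to 1.5 points at 2–5% missing and 1 to 6 points at 10–20% missing, against the planned 15. It is negligible in the first range. It becomes material only from about 10–20% missing, and then chiefly when nurse misclassification differs markedly between arms. The sample size is unaffected. This is a worthwhile, inexpensive improvement and does not put the trial's validity in doubt.

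**What to change.** Amend section 6.2.5 as follows.

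1. In the primary analysis, multiply impute the missing committee verdict from the nurse's daily findings, arm, centre, period and baseline variables. Fit the model in patients who have both assessments, so that arm-specific nurse–committee disagreement and its uncertainty carry through to the result.
2. Keep direct nurse substitution and the all-no-lesion rule as sensitivity analyses.
3. Add a tipping-point analysis that varies the lesion rate among missing verdicts separately by arm, and report where the conclusion changes.

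Nurse and photographic assessments are both planned daily to D10, so no new data are needed. The cost is revised wording and some analysis work. The downside is that the imputation model rests on limited data per centre (48 patients over both periods as planned), and with few missing verdicts it may change the result little.
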